## Abstract

**Background:**

Patients with acute low back pain frequently request diagnostic imaging, and clinicians feel pressure to acquiesce to such requests to sustain patient trust and satisfaction. Spinal imaging in patients with acute low back pain poses risks from diagnostic evaluation of false-positive findings, patient labeling and anxiety, and unnecessary treatment (including spinal surgery). Watchful waiting advice has been an effective strategy to reduce some low-value treatments, and some evidence suggests a watchful waiting approach would be acceptable to many patients requesting diagnostic tests.

**Methods:**

We will use key informant interviews of clinicians and focus groups with primary care patients to refine a theory-informed standardized patient-based intervention designed to teach clinicians how to advise watchful waiting when patients request low-value spinal imaging for low back pain. We will test the effectiveness of the intervention in a randomized clinical trial. We will recruit 8–10 primary care and urgent care clinics (~ 55 clinicians) in Sacramento, CA; clinicians will be randomized 1:1 to intervention and control groups. Over a 3- to 6-month period, clinicians in the intervention group will receive 3 visits with standardized patient instructors (SPIs) portraying patients with acute back pain; SPIs will instruct clinicians in a three-step model emphasizing establishing trust, empathic communication, and negotiation of a watchful waiting approach. Control physicians will receive no intervention. The primary outcome is the post-intervention rate of spinal imaging among actual patients with acute back pain seen by the clinicians adjusted for rate of imaging during a baseline period. Secondary outcomes are use of targeted communication techniques during a follow-up visit with an SP, clinician self-reported use of watchful waiting with actual low back pain patients, post-intervention rates of diagnostic imaging for other musculoskeletal pain syndromes (to test for generalization of intervention effects beyond back pain), and patient trust and satisfaction with physicians.

**Discussion:**

This trial will determine whether standardized patient instructors can help clinicians develop skill in negotiating a watchful waiting approach with patients with acute low back pain, thereby reducing rates of low-value spinal imaging. The trial will also examine the possibility that intervention effects generalize to other diagnostic tests.

**Trial registration:**

ClinicalTrials.govNCT 04255199. Registered on January 20, 2020

## Administrative information

The order of the items has been modified to group similar items (see http://www.equator-network.org/reporting-guidelines/spirit-2013-statement-defining-standard-protocol-items-for-clinical-trials/).

## Introduction

### Background and rationale {6a}

Overutilization is increasingly viewed within the framework of patient safety [1–4]. In primary care, patients with acute low back pain frequently request diagnostic imaging, and primary care and urgent care clinicians feel pressure to acquiesce to such requests to sustain patient trust and satisfaction [5]. Spinal imaging in patients with acute low back pain poses risks from diagnostic evaluation of false-positive findings, patient labeling and anxiety [6], unnecessary treatment (including spinal surgery) with potential downstream complications [7], and added costs. The National Committee for Quality Assurance endorses the inappropriate use of spinal imaging in acute back pain as one of few valid measures of overutilization in primary care [8]. While the Choosing Wisely movement has increased physician awareness, it has not reduced the use of early spinal imaging for acute low back pain [9]. Effective approaches to reducing the use of low-value spinal imaging in primary care are needed.

Watchful waiting advice has been found an effective strategy to reduce low-value treatment (e.g., pediatric ear infections), but its role in reducing low-value testing has received minimal attention. In a Dutch randomized controlled trial, a watchful waiting strategy was acceptable to primary care patients with unexplained symptoms and reduced diagnostic blood testing [10]. In an observational analysis of data from audio-recorded primary care office visits, we found that primary care physicians who advised watchful waiting when patients requested low-value testing were 40% less likely to order the requested test than those who did not use this approach (*p* < .001), and advice to pursue watchful waiting accounted for substantial variance in low-value test ordering (*R*^2^ = 53%) [11]. Meanwhile, psychological theory suggests that physician messages could be tailored to magnify patient acceptance of a watchful waiting strategy [12, 13].

The goals of this trial are to develop a novel educational intervention designed to boost primary care physician skill in delivering a watchful waiting message to patients presenting with acute low back pain, delivered by standardized patient instructors (SPIs), and to test the effectiveness of the SPI-delivered intervention in reducing rates of low-value spinal imaging.

## Objectives {7}

Our study has three specific objectives:

Objective 1: To use key informant interviews of front-line primary care and urgent care clinicians and focus groups with primary care patients to develop and to refine a theory-informed standardized patient (SP)-based intervention designed to teach practicing clinicians how to recommend and negotiate a watchful waiting strategy when patients request low-value spinal imaging for low back pain.

Objective 2: To test in a randomized clinical trial (RCT) the effectiveness of a standardized patient instructor (SPI)-delivered clinician training in increasing the use of watchful waiting among patients with acute low back pain.

We hypothesize that the intervention will (a) reduce rates of lumbar spinal imaging among actual patients with acute back pain seen by clinicians post-intervention (adjusting for pre-RCT rates), (b) increase clinician advice to pursue watchful waiting during a follow-up visit with a regular (non-instructor) standardized patient (SP), (c) increase clinician self-reported use and efficacy of advising watchful waiting with actual low back pain patients, and (d) have no adverse impact on actual patient trust and satisfaction with physicians.

Objective 3: To assess whether intervention effects generalize to other diagnostic tests.

We hypothesize that the SP intervention will (a) decrease rates of neck imaging among actual patients with neck pain seen by study clinicians during the follow-up period (adjusting for pre-RCT rates), (b) decrease rates of overall diagnostic testing (i.e., all diagnostic imaging and blood testing) among adult patients seen by study clinicians during the follow-up period, and (c) increase clinician self-reported use of advising watchful waiting rather than imaging for patients with neck pain and other musculoskeletal pain.

## Trial design {8}

This will be a parallel group randomized trial with primary care clinicians randomized to intervention and control arms. We considered cluster randomization at the clinic level which would reduce risk that intervention clinicians will discuss their experiences with the watchful waiting messages with clinicians randomized to the control arm in the same clinic, potentially introducing contamination of that arm via their social influence on peers. However, recruitment challenges in the context of the COVID-19 pandemic made it difficult to recruit entire clinic staffs to the study simultaneously, which made a clinic-level cluster randomization scheme infeasible. We will therefore randomize clinicians overall 1:1 to intervention and control groups, which allow rolling enrollment and initiation of trial procedures in the context of ongoing pandemic mitigation. The trial is designed as a superiority trial, testing whether the intervention is superior to the control condition in reducing rates of low-value spinal imaging.

## Methods: participants, interventions, and outcomes

### Study setting {9}

We will test the simulated SPI intervention trial among clinicians practicing within 8–10 primary care or urgent care clinics affiliated with two large health systems in Sacramento, CA (USA): the UC Davis Health System and Sutter Health. Together, the two health systems operate over two dozen primary care community-based clinics in the Sacramento metropolitan area, comprising two of the four major health systems serving Sacramento with an estimated market share of 40%.

We will recruit a total of 55 primary care or urgent care clinicians for RCT enrollment. We anticipate enrolling two urgent care sites within the Sutter system where many patients with acute back pain are evaluated; no urgent care sites exist within the University of California, Davis (UCD) system, where we will only enroll primary care clinics.

### Eligibility criteria {10}

For enrollment purposes, “clinicians” are defined as primary care physicians, urgent care physicians, or nurse practitioner/physician assistants who take primary management responsibility for test ordering during routine clinical care. Clinicians will be eligible if they intend to practice at least 50% of a full-time equivalent (FTE) in adult primary care or urgent care in one of the target clinics for the trial duration and have been in active in at least 50% FTE practice within the health system for at least 2 years prior to enrollment (to enable collection of baseline testing rates). We will not include clinicians practicing < 50% FTE because of the need to accrue sufficient numbers of actual back pain patients during pre- and post-intervention phases for well-powered analyses of the primary outcome of lumbar spinal imaging ordering (see the “Sample size {14}” section). To achieve the desired sample size, we will seek to enroll clinicians from 8 to 10 primary care or urgent care clinics.

To help achieve objective 1 (developing and refining the intervention content), we have conducted key informant interviews with seven front-line clinicians. In the interviews, we elicited clinician feedback about the challenges posed in avoiding low-value imaging in patients with acute low back pain and the suitability of the study intervention in promoting effective clinician-patient communication regarding low-value spinal imaging. For key informant interviews, we recruited clinicians from within and outside the UCD Health System whom we believed would provide constructive insights. We anticipate completing at least two additional key informant interviews with clinicians. Clinicians who provided key informant interviews will not be eligible to enroll in the RCT.

We have also completed 6 patient focus groups to help achieve objective 1. For patient focus groups, we recruited English-speaking patients aged 18–65 years who had seen a primary care clinician for acute low back pain in the past 2 years. Patients were ineligible if they had chronic, persistent back pain or a history of spinal surgery. Patients were recruited using Craigslist and the UC Davis Health StudyPages website [14]. Due to the COVID-19 pandemic, we completed all focus groups online using the Zoom platform with a median of 5 patient attendees per group (*n* = 30 patients). The goal of these focus groups was to elicit patient feedback regarding the barriers and facilitators to accepting physician advice to pursue a watchful waiting strategy regarding lumbar spinal imaging. We also elicited feedback about how patients might react to specific watchful waiting messages in the context of low back pain. We plan no additional focus groups as we achieved data saturation with the completed focus groups.

### Who will take informed consent? {26a}

Research staff obtained or will obtain informed verbal assent from all potential participants prior to enrolment, including clinician enrollees for the RCT, clinician key informants for telephone interviews, and patients enrolled in focus groups. Research staff will offer enrolment to potential clinician enrollees during staff meetings. Potentially interested clinicians will receive the IRB-approved consent form via email and will provide verbal assent by either replying to the email affirmatively or by calling our research coordinator. The IRB approved omission of obtaining signatures on consent forms. Likewise, we emailed consent forms to clinician key informant and patients participating in focus groups, and these participants provided verbal assent prior to the beginning of interviews or focus groups, respectively.

### Additional consent provisions for collection and use of participant data and biological specimens {26b}

Not applicable as this trial does not involve collecting biological specimens for storage.

## Interventions

### Explanation for the choice of comparators {6b}

We will compare outcomes between clinicians assigned to receive an active intervention involving three simulated visits with an SPI portraying a patient with acute back pain and clinicians assigned to no intervention. We opted for a passive rather than an active control condition for several reasons. First, we believe it is unlikely that the SPI visits alone without the communication content (i.e., an attention control) would affect clinician communication behaviors or subsequent test ordering. Second, we believed that implementation of an attention control would be unacceptable to clinic administration due to loss of productivity stemming from these additional scheduled visits, as SP visits use appointment slots reserved for actual patients. Third, we were concerned that clinicians randomized to the control arm would object to participating in attention control visits, which might lead to clinician attrition. After completion of data collection, we will offer clinicians in the control arm the opportunity to receive one simulated office visit with an SPI so that clinicians in the control can be instructed in the intervention communication strategies.

### Intervention description {11a}

Clinicians randomized to the control group will receive no intervention during the trial period.

Clinicians randomized to the intervention group will receive three visits over a 3- to 6-month period with an SPI scheduled during normal clinic hours for 20-min in-person office visits. (Due to the COVID-19 pandemic, clinicians may opt to have the second or third SPI visits as video visits, although we will require that the initial SPI visit be conducted in-person.) Clinicians will be aware that they are scheduled to see a standardized patient, and the SPI will begin the visit by reminding the clinician that they are an SP and orienting the clinician to the overall visit plan. During each visit, SPIs will spend 10–12 min portraying a patient with acute back pain based on pre-specified role profiles. During this time, SPIs will assess clinicians’ performance on a three-step intervention model for communicating a watchful waiting message regarding spinal imaging that is based on psychological theory [15–17], extant literature and preliminary studies [18–22], key informant interviews with clinicians, and focus groups with patients (Table 1). We consider the model to be preliminary at this stage, as we may modify content based on additional key informant interviews or our experience during SPI training and intervention pilot testing.

**Table 1 Tab1:** Watchful Waiting to Avoid Inappropriate Testing (WAIT): intervention model with key skills and criteria for fulfillment

Step	Key skills	Criteria for fulfillment with examples (to guide intervention content and coding)
1. Set the stage for deferred imaging by building trust	1. Demonstrate openness and interest 2. Avoid interruptions 3. Identify the patient’s motivating concern or expectations	1. Non-verbal openness and engagement • Sits, orients toward the patient • Maintains open body position, leans in • Frequent, attentive eye contact • Engaged facial expressions or gestures (e.g., nodding) 2. Clinician does not interrupt early on. Allows patient to “tell their story” without cutting them off. 3. Clinician probes or asks for more information when patient signals a major underlying or motivating concern or expectations: “It sounds like you are worried that you seriously injured your back. Is that right?” or “You seem to be concerned that you need an MRI. Can you tell me more about that?”
2. Convey empathy	1. Legitimize patient’s concerns 2. Name and explore patient’s emotions 3. Express your understanding 4. Make supportive statements 5. Praise patient’s attempts to address pain	1. Legitimizing statements: “I can understand why you are concerned.” 2. Naming and exploring emotions: “You said you are afraid. Can you tell me more about what you are afraid of?” 3. Expressing understanding: “This is obviously a tough thing to go through. I can see that it’s really impacted your work life.” 4. Supportive statements: “I’m committed to helping you find a workable solution.” 5. Praise: “I think it’s great that you have been trying to get out and walk.”
3. Communicate optimism and openness while advocating a plan without imaging	1. Convey *optimism* when sharing your assessment and suggested plan, emphasizing reassuring aspects of the history and physical examination and the patient’s favorable prognosis. 2. Advocate a conservative treatment plan without imaging 3. If a patient asks about imaging, recommend a watchful waiting approach 4. Communicate your *availability* if the patient’s pain does not improve.	1. Frames diagnosis and treatment recommendation in an optimistic, positive frame: “Overall, I’m actually quite reassured by your history and physical. I do not see any signs of a disc problem or nerve involvement, and I’m confident that your back pain is very likely to improve markedly over the next couple of weeks.” 2. Confidently endorses an initial treatment plan that does not include imaging EX: “Given your reassuring history and exam, I’m confident that you’ll improve with conservative treatment, and in these cases, I do not recommend imaging at this time.” 3. If the patient asks about imaging, clinician advocates a “watchful waiting” approach: EX: “I do not recommend imaging at this point, but I’d consider it in a few weeks if your pain did not improve substantially, as I expect it to.” 4. Articulates a follow-up, contingency plan for what the patient should do if the pain or other symptoms worsen or do not improve. Plan should address *how* the patient should contact the clinician, *when* they should do so, and *what* the clinician is likely to do in response. (The follow-up plan may or may not include a plan for deferred imaging.) EX: “If you are pain is not substantially improved within two weeks, I’d like you to contact me via MyChart. I can then order you an x-ray and then we can have a either a phone call or a video visit.”

Titled Watchful Waiting to Avoid Inappropriate Testing (WAIT), our intervention model has three steps: (1) set the stage for deferred imaging by building trust, (2) convey empathy, and (3) communicate optimism while advocating a plan without imaging. We plan to emphasize steps 1 and 2 during the initial in-person SPI visit, which will allow the SPI to evaluate the clinicians’ use of non-verbal communication skills (step 1) and to elaborate the various ways clinicians can communicate empathy (step 2). In the second and third visits, SPIs will emphasize the skills in step 3, which involve negotiating a plan that does not include spinal imaging. To assist clinicians in grasping and remembering the skills in this step, SPIs will teach the following key words: *optimism*, *advocacy*, and *availability*. These words encapsulate the critical elements of this step, as the literature and our preliminary qualitative studies suggest that patients will accept a plan without imaging if it is confidently endorsed by the clinician, if they are provided immediate treatment options, and if the clinicians demonstrate availability and willingness to consider imaging if symptoms do not improve.

### Criteria for discontinuing or modifying allocated interventions {11b}

Clinicians will be analyzed according to their initial allocation. Modifying allocation will not be allowed.

### Strategies to improve adherence to interventions {11c}

Clinicians receiving standardized patient visits will have reduced productivity during these clinic sessions, as the standardized patient appointment will take appointment slots that could have been used by actual patients. We will therefore compensate clinicians with the equivalent of $125 in Relative Value Units (RVUs) per visit, which are used widely in the USA, to measure clinician productivity and to determine incentive compensation. We have arranged this remuneration through the participating health systems.

### Relevant concomitant care permitted or prohibited during the trial {11d}

None.

### Provisions for post-trial care {30}

None.

### Outcomes {12}

The *primary outcome* will be the rate of lumbar spinal imaging [x-ray, computed tomography (CT), or magnetic resonance imaging (MRI)] among adult patients (age ≥ 18 years) with acute back pain seen by study clinicians during an 18-month follow-up period, adjusted for the clinician’s baseline imaging rate during a 24-month pre-randomization phase. The numerator for the rates will be the number of lumbar spinal imaging tests completed, and the denominator will be the total number of patient visits with a diagnosis of acute back pain during the relevant study period. To identify this outcome, we will collect automated data from the electronic medical records of all patients seen by study physicians during the 18-month post-intervention follow-up period, as well as the 2-year period prior to the intervention (to allow for adjustment for baseline utilization). In a pilot trial [21], we abstracted testing data within 34,949 actual adult patient visits among 61 primary care physicians before and after an SPI intervention. We will pursue a similar approach here, assessing visit-level utilization of the following imaging tests: lumbar spinal MRI/CT and lumbar spinal radiography. Visits will include both in-person and telemedicine/video visits given the increased use of the latter during the COVID-19 pandemic (identified using Healthcare Common Procedure Coding System codes G2010, G2012, G2061-2063; Current Procedural Terminology codes 99421-99423, 99431, 99441-99443; 99201-99215 with a GT-95 modifier). We will collect longitudinal data on International Classification of Diseases (ICD)-9/10 diagnoses to allow identification of subsets of patients presenting with acute back pain based on the absence of back pain diagnoses on visits in the prior 6 months (ICD-9-CM: 723.1, 724.x, or ICD-10: M54.2, M54.5, M54.6, M54.89) and the inclusion of a back pain diagnostic code in the primary position on the claims, consistent with the Healthcare Effectiveness Data Information Set (HEDIS) overuse measure related to low back pain imaging [8]. We will also collect patient-level covariates to enable stratified analyses, adjustment (e.g., age, sex, available race/ethnicity, any Medicaid insurance), and restriction of analyses to patients aged 18–50 years consistent with the HEDIS overuse measure [8]. We will assess post-intervention rates of clinician ordering of both plain x-ray and advanced spinal imaging (MRI/CT).

*Secondary outcomes* will include:
The post-intervention rate of cervical spinal imaging among adults adjusted for baseline rate (to examine the potential for the intervention effects to generalize beyond the management of low back pain (objective 3)). We will compute this analogously to the rate of lumbar spinal imaging but only among patients with “neck pain” diagnoses in the primary position using ICD-9 and ICD-10 codes [23, 24].The rate of overall diagnostic testing among adult patients adjusted for baseline. For these analyses, we will identify counts of diagnostic tests ordered during primary care visits participating clinicians during the 24-month period prior to their first SPI visits and from the date of their final SPI visits through up to 18 months, consistent with our pilot trial [21]. Specifically, we will include visit-level counts of the following diagnostic test categories: hematology and chemistry, urine and body fluid analyses, microbiology, imaging tests (subcategorized as non-spine plain x-ray or sonography, spinal x-ray, non-spine MRI or CT, neuroimaging), electrocardiography, other cardiac tests, and miscellaneous tests (e.g., nuclear medicine). We will exclude tests performed for screening or prevention (e.g., lipid or diabetes mellitus tests, bilateral screening mammograms). Both UC Davis and Sutter utilize the same EMR system (Epic), and so we expect to be able to harmonize patient and visit EMR data extracted from the two systems. The analysts compiling these data will be blinded to the study arm.The post-intervention rate of test *ordering* which is distinct from test *completion*. These outcomes will be computed similarly as the test completion outcomes specified above, but we will use a signifier in the electronic medical record that a given test was ordered by the clinician. Because not all ordered tests are completed by patients, we assess test ordering as a secondary outcome.Approximately 7–9 months after clinician enrolment (and after all intervention visits are completed among intervention physicians), intervention and control physicians will receive a visit by a single non-instructor SP portraying a patient with acute low back pain. Using SP observations and audio-recordings of these visits, we will ascertain as a *secondary outcome* the extent to which clinicians implemented various steps of the model. We will use iterative systematic content analysis of transcripts from audio-recorded visits to quantify how frequently clinicians engaged in the specific steps emphasized in the intervention, as well as the overall extent to which clinicians implemented watchful waiting. To guide coding, we will develop a manual to guide trained research assistants in coding transcriptions while simultaneously listening to audio-recorded visits. As the first step in the model addresses non-verbal communication, we will also incorporate standardized patient ratings on non-verbal communication. Coders will be blinded to clinician allocation. To the extent possible, we will blind SPs to the intervention group, but given the small number of total SPs, some SPs may revisit clinics where they previously performed the role of intervention SPIs, thereby making SP blinding difficult if not impossible without training and hiring entirely new SPs for the assessment phase. Inter-observer agreement for coding targeted behaviors will be assessed using Cohen’s kappa, and disagreements will be resolved by consensus or by review of the audio-recording by a third party. We have successfully used this process to assess physician-patient interaction in other studies [19, 21]. Ultimately, this process will generate a summary scale expressing the extent to which clinicians engaged in intervention steps during SP visits.Six months after final SPI visits, we will survey randomized clinicians regarding the use of watchful waiting when actual back pain patients request low-value spinal imaging. We will also survey physicians regarding the use of watchful waiting for neck pain, other regional musculoskeletal pain syndromes (e.g., shoulder and knee pain), and in other contexts (e.g., when patients request antibiotics). For intervention clinicians, the survey will also inquire regarding clinicians’ views on the quality, acceptability, and utility of the SPI training. Clinician self-reported use of watchful waiting during the follow-up period will constitute a *secondary outcome* of the trial.To address concerns that a watchful waiting strategy might undermine patient trust and confidence in physicians, we will assess as a *secondary outcome* for potential adverse impacts of the intervention on patient experience. To develop this measure, we will link study physicians to pre- and post-intervention patient experience data collected by the health systems as part of routine care. We have confirmed the feasibility of such linkage with UC Davis executives and are exploring this possibility within the Sutter system. These measures include visit-level Consumer Assessment of Healthcare Providers and Systems (CAHPS) results [25], which we will use to develop pre- and post-intervention summary measures of patient experience. Analyses will assess for adjusted differences in post-intervention patient experience measures among intervention physicians as compared to control physicians, after adjustment for baseline patient experience.

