Our analysis plan will assess whether the intervention affects other test ordering, potentially because clinicians generalize lessons learned in counseling acute back pain patients to other patients with complaints that prompt consideration of low-value tests (e.g., neck pain). A finding that the intervention affects both the primary and secondary outcomes would be particularly significant, as the attractiveness of the intervention to health systems and policymakers would be much greater if intervention effects are not isolated to low back pain imaging. If our trial finds significant impacts on both primary and secondary utilization outcomes, then results would justify confirmatory trials and dissemination attempts with non-randomized evaluations.

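### The overall-testing outcome meant to show spread to other tests also counts lumbar imaging from the primary outcome, and does not say where spinal MRI/CT belongs

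*Protocol article*

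**What the plan says.** Objectives {7} gives the aim of objective 3 as "To assess whether intervention effects generalize to other diagnostic tests". Hypothesis (b) under it is that the intervention will "decrease rates of overall diagnostic testing (i.e., all diagnostic imaging and blood testing) among adult patients seen by study clinicians".

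Outcomes {12} builds this secondary outcome from "counts of diagnostic tests ordered during primary care visits participating clinicians", before and after the intervention. Its imaging part is "subcategorized as non-spine plain x-ray or sonography, spinal x-ray, non-spine MRI or CT, neuroimaging". One exclusion is stated: "We will exclude tests performed for screening or prevention". Nothing removes lumbar imaging or visits for back pain.

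The primary outcome in the same section is the "rate of lumbar spinal imaging [x-ray, computed tomography (CT), or magnetic resonance imaging (MRI)] among adult patients" with acute back pain, for the same clinicians over the 18-month follow-up.

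The Discussion says that the appeal of the intervention to health systems and policymakers "would be much greater if intervention effects are not isolated to low back pain imaging". It adds that significant effects on both primary and secondary utilization outcomes would justify confirmatory trials and attempts at dissemination.

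**The concern.** An outcome that is to show an effect on other tests should not contain the targeted test. Here it does. An intervention that lowered lumbar x-ray use at acute back pain visits and changed nothing else would still lower the overall-testing count. The Discussion treats an effect on the primary outcome together with effects on secondary utilization outcomes as stronger evidence than the primary result alone, which requires the two to be separable.

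The second weakness is one of definition. The imaging list names spinal x-ray and non-spine MRI or CT, but does not say where spinal MRI/CT goes. How much of the primary outcome is counted again depends on that. The Discussion itself expects some difficulty in extracting equivalent data from the two health systems, so an unassigned modality could be handled differently in each.

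**Working it through.** **The plan's own figure.** Sample size {14} gives 80.1% power. Its inputs are 25% imaging under control, a 7-point fall to 18%, 8 × 6 = 48 clinicians (24 per arm at 1:1), 57 pre- and 35 post-intervention patients each, and a two-sided 5% test. A normal approximation for the arm-by-period interaction on the logit scale, with clinic and clinician intercepts cancelling in the pre/post contrast, gives:

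- Variance = 2/(0.25 × 0.75 × 24 × 57) + 1/(0.25 × 0.75 × 24 × 35) + 1/(0.18 × 0.82 × 24 × 35) = 0.00780 + 0.00635 + 0.00807 = 0.0222, so SE = 0.1490.
- Effect = ln(0.25/0.75) − ln(0.18/0.82) = 0.4177.
- Power = Φ(0.4177/0.1490 − 1.96) = Φ(0.843) = 80.0%.

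Logit or risk-difference versions that shrink the residual variance by 4% or 5% for the stated correlations give 78.6% to 82.0%. Other versions (risk difference without that factor or with null variance, or a Poisson log scale) give 71% to 77%. The point does not depend on this figure. The check only shows that 7 points and 35 visits fit together as the planned effect.

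**Does the overlap exist?** Four features of the text settle it:

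- Clinicians: the same in both outcomes.
- Period: post-intervention follow-up of up to 18 months in both.
- Visits: acute back pain visits for the primary outcome; primary care visits generally for overall testing, with back pain visits not removed.
- Tests: lumbar x-ray, CT or MRI for the primary outcome; for overall testing, a list with spinal x-ray in it and only screening or preventive tests taken out.

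A lumbar x-ray at a primary care visit for acute back pain therefore enters both.

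**How much is counted twice?** Taking one image per imaged visit:

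- Expected images per clinician under control: 35 × 0.25 = 8.75.
- Images avoided at the planned effect: 35 × 0.07 = 2.45, leaving 6.30.

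The figure of 2.45 is an upper limit for the planned effect. The 7 points refer to spinal imaging as a whole, so if spinal MRI/CT is outside the overall count, only the x-ray part carries over.

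**Share of the total.** The relative fall with no generalization at all is 2.45/(V × t), where V is visits per clinician and t is tests per visit. The article gives neither for this trial. V is assumed to run from 573 to 5,000; the lower end is the pilot's 34,949/61 = 573 (Outcomes {12}). The range for t, 0.3 to 2, is also assumed.

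- V = 573, t = 0.3: 2.45/171.9 = 1.4%.
- V = 573, t = 0.5: 2.45/286.5 = 0.86%.
- V = 573, t = 1.5: 2.45/859.5 = 0.29%.
- V = 5,000, t = 2: 2.45/10,000 = 0.02%.

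**Share of a spinal-imaging subtotal.** The relative fall is 2.45/(8.75 + S), where S is the number of other spinal images per clinician, assumed to be 0 to 35.

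- S = 0: 2.45/8.75 = 28%.
- S = 8.75: 2.45/17.5 = 14%.
- S = 35: 2.45/43.75 = 5.6%.

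These subtotal figures include all modalities. The article gives no split of lumbar imaging into x-ray and MRI/CT, so a spinal x-ray figure cannot be worked out separately.

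**The case against.** The strongest reply is that the outcome is what its name says. Hypothesis (b) is about overall testing and covers all imaging and blood tests, so an all-inclusive count answers it as worded. That stands as a defence of reporting the total. It does not make the total a clean answer to the objective above it, which is about other tests.

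Generalization also has separate evidence. Cervical imaging is analysed among patients with a primary neck pain diagnosis, and clinicians report their use of watchful waiting for neck and other musculoskeletal pain. This stands, and it limits what is at stake. It also shows that the protocol separates the targeted condition from the rest in one objective 3 outcome and not in the other.

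The size is the third reply. A carry-over of at most about 1.4% of the total is unlikely to produce a significant result by itself. The calculation also leans high: it carries over every modality, and it sets 35 post-intervention visits against a pilot volume that covers time before and after the pilot intervention and is no forecast for this trial. All of this stands.

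Three stronger readings are tempting but are not supported:

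- *Spinal MRI/CT is left out of the count.* The term neuroimaging is undefined and could hold it, and Objectives {7} speaks of all diagnostic imaging. Only its place is unclear.
- *That gap causes the overlap.* The direction is the reverse: leaving spinal MRI/CT out would reduce the overlap, and including it would increase it.
- *A fall in spinal x-rays will be presented as spread to other tests.* The article plans no separate test of that subcategory; it appears only as a component of the count. Results by category would help a reader see where a fall came from.

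**Conclusion.** The point holds in a limited form. The overall-testing outcome serves an objective about other tests, yet it includes lumbar x-rays that also count towards the primary outcome, and the article does not say which category holds spinal MRI/CT. That much follows from the text without assumptions.

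The size does rest on assumptions. At the planned effect, the double counting is at most 2.45 images per intervention clinician: about 0.02% to 1.4% of the total over the assumed visit volumes and testing rates, and about 6% to 28% of a spinal-imaging subtotal over the assumed counts of other spinal images. A reader might infer that the planned overall result is seriously contaminated; these figures do not support that. The primary analysis and its stated power are unaffected. Severity is minor, and the change is a free improvement.

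**What to change.** - For objective 3, analyse the count of non-screening tests with lumbar spinal imaging of every modality removed, using the same model and periods as now planned.
- Keep all other tests at back pain visits. Removing those visits altogether is unnecessary and would discard real generalization, such as fewer blood tests ordered there.
- Report the all-inclusive count alongside it as descriptive.
- State which category holds spinal MRI/CT, and apply the same mapping in both health systems.

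The cost is one filter in the code that builds the analysis dataset and a sentence or two in the outcome definition. Lumbar x-ray and lumbar MRI/CT are already to be identified at visit level for the primary outcome, so no new data are needed. The sample size does not change.
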